### 3.2. Secondary Objective(s) and Endpoint(s)

The first secondary objective is to demonstrate that the risk of false-negative diagnosis with the 4PEPS strategy is very low in accordance with the ISTH criteria for validation of rule-out PE diagnostic strategies. The endpoint will be the false-negative rate defined as the rate of thromboembolic events occurring in the 90 days following inclusion in patients for whom PE was ruled out according to the 4PEPS strategy and who were not treated with anticoagulants. ISTH recommendations state the upper limit of the 95% confidence interval (95%CI) of this 90-day thromboembolic event rate should be less than 1.82 + 0.00528* prevalence, i.e., a rate ≤1.89% for a prevalence of 14% [16].

The second secondary objective is to demonstrate that the 4PEPS strategy (intervention group) is not inferior to current practices (control group) as regards the risk of false-negative diagnosis. The false-negative rate will be defined as the rate of thromboembolic events occurring in the 90 days following inclusion in patients for whom PE was ruled out and who were not treated with anticoagulants. 

The other secondary objectives are to evaluate and compare to usual practice the impact of the 4PEPS strategy as regards the rate of D-dimer measurement and the length of time spent in the emergency department by patients with suspected PE.

The ancillary objectives are to assess the rate of incidental findings on CTPA, the acceptance by physicians and their use in everyday practice of the clinical decision support tool SPEED [23], as regards the rate of patients for whom the SPEED application is used in real time (i.e., when the data that enable the automatic calculation of the clinical probability and the reminder of the appropriate diagnostic strategy have been entered before any additional examinations are performed, in particular, the D-dimer test); and to evaluate the appropriateness of diagnostic management according to international guidelines and if it differs when the SPEED application is used in real time or not. 

We will also evaluate and compare to usual practice the medico-economic impact of the 4PEPS strategy in terms of cost per serious clinical event related to the diagnostic procedure avoided in the 90 days following inclusion (cost–efficacy analysis). The endpoint will be the differential cost–efficacy ratio at 90 days.

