### 6.2. Strategy under Study: Interventional Group

Physicians of the participating centers in the intervention group will have the recommendation to apply the 4PEPS strategy. To make it easier to apply, the 4PEPS score will be included in SPEED [23]. Investigators will be asked to enter the information relating to patients included in the study directly into SPEED before performing any testing. Entering these data will enable the 4PEPS score to be calculated automatically and specific recommendations to be provided. A paper version of the CRF will also be available.

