## 9. Statistical Analysis

### 9.1. General Considerations 

Population characteristics will be described using their mean/standard deviation, median/interquartile range, or percent/95% confidence interval, as appropriate. Univariate comparisons will be made using Student’s, Mann–Whitney, or Fisher’s exact tests, as appropriate. The alpha risk will be set at 5%. All tests will be one-sided. Given that some proportions are expected to be small, confidence intervals will be calculated using the Clopper and Pearson exact method. 

The analysis will be performed using R software (R Foundation for Statistical Computing; 2008. http://www.R-project.org (accessed on 1 November 2022)) and its PropCIs and MASS add-ons (http://CRAN.R-project.org/package=PropCIs (accessed on 1 November 2022)). All objectives will be analyzed on the overall included population (intention-to-treat). A complementary per-protocol analysis will be performed, especially for the 4PEPS strategy in the interventional group. 

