### 9.3. Secondary Statistical Analysis

The confidence interval of the false-negative rate with the 4PEPS strategy will be calculated on an intention-to-treat basis and then on a per-protocol basis, and its upper limit will be compared with the limit considered acceptable by the ISTH recommendations based on the prevalence in the study: 1.82 + 0.00528* prevalence, i.e., for a prevalence of 14%, an upper limit ≤1.89% [16]. 

Hierarchical analysis of the other secondary outcomes will be conducted using a mixed effects logistic regression. If the primary safety endpoint and then the primary efficacy endpoint are confirmed, the false-negative rate with the 4PEPS strategy will be compared to that of the usual approaches in the control group using a mixed-effects logistic regression with a non-inferiority limit set at 1.35% [27]. If this endpoint is confirmed, then the two other secondary endpoints will be analyzed using the Holm procedure for multiple testing correction.

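### The 4PEPS false-negative rate leaves out untreated-only exclusions that matter: PE found by scanning despite a 4PEPS rule-out normally drops out, so the rate is probably biased downward as a validation of the strategy

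*Protocol article*

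**What the plan says.** Section 3.2 of the protocol article sets the first secondary objective: "to demonstrate that the risk of false-negative diagnosis with the 4PEPS strategy is very low", judged by the ISTH criteria for validating rule-out strategies. The endpoint is the 90-day thromboembolic event rate "in patients for whom PE was ruled out according to the 4PEPS strategy and who were not treated with anticoagulants". The upper 95% confidence limit is to be compared with 1.82 + 0.00528 × prevalence, which the protocol puts at 1.89% for a prevalence of 14%.

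Section 9.3 gives the analysis sets: "The confidence interval of the false-negative rate with the 4PEPS strategy will be calculated on an intention-to-treat basis and then on a per-protocol basis". Section 9.1 adds that "confidence intervals will be calculated using the Clopper and Pearson exact method".

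Adherence is voluntary. Section 6.2 states: "Physicians of the participating centers in the intervention group will have the recommendation to apply the 4PEPS strategy".

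Section 12 gives the rationale. Follow-up events in untreated patients regarded as PE-free are the usual yardstick for exclusion strategies, and this analysis complements the main ones.

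**The concern.** The objective is about the 4PEPS strategy, but the rate depends on what the physician did after the 4PEPS result. Take a patient whom 4PEPS rules out and whom the physician scans anyway.

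- If the scan is negative and no anticoagulant is given, the patient can remain in the denominator as a correct rule-out.
- If the scan shows PE, 4PEPS was wrong, but the patient is normally anticoagulated and leaves both numerator and denominator.

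That asymmetry lowers the rate. If the definition is instead read as covering only patients managed as 4PEPS advised, all overridden patients leave. These are plausibly the patients of greater concern, so the selection probably still runs downward.

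Nothing else in the protocol counts the missed case. The primary safety endpoint in Section 3.1 takes thromboembolic events in patients not diagnosed in the emergency department, or new events in those who were; the initial PE shown by an override scan is neither. At stake is whether meeting the ISTH limit can be presented as validating 4PEPS, or only 4PEPS as used by physicians who sometimes overrule it.

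**Working it through.** **Inputs from the protocol.** Intervention arm 1280; loss or non-analysable 5%; PE prevalence 14%; event rate after rule-out 0.8% (all Section 10.1). Imaging rate in the intervention group 36% (Section 10.2). Clopper-Pearson intervals and one-sided tests (Section 9.1). Because Section 3.2 refers to a 95% confidence interval, two-sided and one-sided upper limits are both shown.

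**Not in the protocol, assumed here.** Override rate 5% to 20% of imaging-free rule-outs; PE yield of override scans 1% to 5%.

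**Step 1: the plan's limit.** 1.82 + 0.00528 × 14 = 1.894%. The stated 1.89% is reproduced.

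**Step 2: the planned rate.** Analysable patients: 1280 × 0.95 = 1216. Ruled out and untreated, approximated by those without PE: 1216 × 0.86 ≈ 1046. Events: 0.008 × 1046 ≈ 8. The Clopper-Pearson upper limit for x events in n patients is the 0.975 quantile (two-sided) or 0.95 quantile (one-sided) of Beta(x + 1, n − x). For 8/1046 = 0.76% it is 1.50% or 1.38%. Both pass.

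**Step 3: add override PEs.** Imaging-free rule-outs: 0.64 × 1216 ≈ 778. Override PEs = 778 × override rate × yield, rounded and added to numerator and denominator, supposing that they come on top of the expected 8.

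| Override rate | Yield | PEs added | Rate | Upper limit, two-sided | Upper limit, one-sided |
|---|---|---|---|---|---|
| 5% | 1% | 0.39 → 0 | 8/1046 = 0.76% | 1.50% | 1.38% |
| 10% | 2% | 1.56 → 2 | 10/1048 = 0.95% | 1.75% | 1.61% |
| 20% | 2% | 3.11 → 3 | 11/1049 = 1.05% | 1.87% | 1.73% |
| 10% | 5% | 3.89 → 4 | 12/1050 = 1.14% | 1.99% (fails) | 1.85% |
| 15% | 5% | 5.83 → 6 | 14/1052 = 1.33% | 2.22% (fails) | 2.07% (fails) |
| 20% | 5% | 7.78 → 8 | 16/1054 = 1.52% | 2.45% (fails) | 2.30% (fails) |

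**Step 4: break-even.** Four added PEs fail the two-sided limit (12/1050, 1.99%). Five fail the one-sided limit (13/1051 = 1.24%, upper limit 1.96%). Three pass either way.

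**Step 5: if the override PEs are already among the 8.** The complete count stays 8/1046 with upper limit 1.50%, and the planned rate would be lower still; with four removed it is 4/1042 = 0.38%. The bias is then present but does not change the conclusion.

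**The case against.** **The wording is not watertight.** Almost everyone with a confirmed follow-up event is then anticoagulated, so the exclusion cannot sensibly cover treatment started because of the event. Read as untreated at the time of rule-out, it might let an override PE count. This stands as an ambiguity. The protocol does not say that such a PE counts, however, and Section 12 describes the method in patients regarded as free of PE, which a patient with PE on the index scan is not.

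**The convention is established.** That is true, and it is a reason to keep the planned rate. The convention is most informative where management follows the rule, and here following it is voluntary.

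**The limit belongs to a 90-day event rate.** Override scans can detect subsegmental or false-positive PE, a risk that the Introduction itself raises, while patients not scanned are judged by symptoms. Counting every override PE could bias against 4PEPS. This also stands, so the added rate should not be a compulsory hurdle.

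**The scenarios are assumed, and the counts may overlap.** The 0.8% carries the same citation as the retrospective assessment of 4PEPS and may already be its total miss rate; that source is not available here. Step 5 shows the consequence.

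**The role is limited.** Section 12 treats this rate as complementary, and Section 9.3 makes no other test depend on it.

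A reader might also infer that the per-protocol analysis discards these patients as deviations. Sections 9.1 and 9.3 do not define that set, so this cannot be asserted; equally, nothing there says that the cases are counted.

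**Conclusion.** The concern holds in a limited form. On the natural readings, a PE found at the index work-up by scanning against a 4PEPS rule-out is normally excluded from the rate compared with 1.89%. The rate then describes 4PEPS together with physician override and is probably biased downward as a validation of the strategy.

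The size is unknown. Under the assumed ranges, about 0.4 to 8 such PEs would be left out. If they add to the expected 8/1046, four (two-sided) or five (one-sided) reverse the expected pass; fewer do not, and if they overlap with the 8 the pass remains.

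It would be tempting to say that every such PE drops out, that the bias always favours 4PEPS, or that the planned test would validate a rule that in truth fails. The protocol does not support this. A detected PE left untreated would not be excluded, the definition has more than one reading, and neither override rate nor yield is given.

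**What to change.** Keep the planned rate, and state that its anticoagulant exclusion covers only treatment given for reasons other than confirmed VTE, so that treatment of an event never removes the event.

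Add one sensitivity analysis in the intervention group:

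- Classify all patients by the recorded 4PEPS result (score plus D-dimer), whatever was done next.
- Count as false negatives any VTE confirmed at the index work-up or within 90 days.
- Show subsegmental PE separately, and report the override rate.

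If the two rates fall on different sides of the ISTH limit, restrict the conclusion to 4PEPS as applied with physician override.

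The classification needs one set of category boundaries. The Introduction and Table 1 place scores of 5 and 12 in different categories, and these passages must be reconciled first.

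The cost is some wording and one analysis on data that Sections 6.2 and 7 already collect, with no added patients or visits. The downside is that the added rate is an upper bound, because some override-detected PEs might never have become symptomatic.

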## 4. Study Settings and Population

### 4.1. Centers

Twenty centers will be selected based on their participation in previous trials on PE diagnosis in emergency departments and their possibility of recruitment.

Inclusion criteria for study participants

Admission to an emergency department participating in the study.Suspected PE due to thoracic symptoms (dyspnea, chest pain, or hemoptysis) and/or syncope without any other obvious explanation after clinical examination and possible additional first-line tests (ECG, chest X-ray, or routine lab work-up not including D-dimer test).Free, prior, and informed consent to participate in the study.

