## 3. Study Objectives and Endpoints

### 3.1. Primary Objective and Endpoints 

The primary objective is to demonstrate that the application of the 4PEPS strategy by the emergency physicians in comparison to current practices (i) does not increase the risk of serious events related to diagnostic strategies and (ii) significantly reduces the use of thoracic imaging. 

The primary safety endpoint will be the rate of serious events in the 90 days following inclusion:Serious adverse events related to diagnostic testing (leading to hospitalization or prolongation of hospitalization, permanent inability or incapacity, and death).Symptomatic thromboembolic events in patients not diagnosed with PE in the emergency department or new thromboembolic events in patients diagnosed with PE.Death related to PE (initial or recurrent PE).Major bleeding related to the anticoagulant treatment prescribed for pulmonary embolism according to ISTH criteria [21].

All events must be symptomatic, documented, and confirmed by the clinical adjudication committee blinded to the study group. For analysis of deaths in cases where an autopsy is not performed, a precise definition of the elements indicating that the death is possibly related to pulmonary embolism will be used according to recent ISTH proposals [22].

The primary efficacy endpoint will be the rate of thoracic imaging among all included patients with suspected PE. A relative reduction of at least 20% is expected.

The following thoracic examinations will be considered if they are performed at the request of the emergency physician in search of PE and this during the passage in the emergency department and/or within 72 h of inclusion:CTPA.Planar perfusion or perfusion–ventilation pulmonary scintigraphy.SPECT scintigraphy.

The examinations have to be mentioned in the patient’s record and be the subject of a report, with analysis of the file taken as proof of this. 

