### 4.2. Non-Inclusion Criteria for Study Participants

Age < 18 years.Known result of a specific diagnostic examination for PE (D-dimer test, thoracic CT angiography, pulmonary scintigraphy, or venous ultrasound of the lower limbs).Hemodynamic instability (systolic blood pressure < 90 mmHg or more than 40 mmHg lower than usual for more than 15 min).Curative dose of anticoagulant in place for more than two days prior to inclusion.3-month follow-up not possible.Pregnant or parturient patient.Patient in detention by judicial or administrative decision.Patient undergoing compulsory psychiatric treatment.Patient placed under a legal protection measure.Patient incapable of giving free and informed consent.

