## 5. Experimental Plan and Randomization

SPEED&PEPS will be an open-labelled cluster-randomized study, with 10 centers being allocated to the control group and 10 centers to the interventional group. Before randomization, participating centers will perform a preliminary assessment of the number of patients being investigated for suspected PE per month and of the rate of imaging test performed in patients suspected of PE in order to have an accurate idea of their baseline status [20]. These two criteria will be applied as stratification criteria during randomization to assure comparability between groups. 

SPEED&PEPS will be a pragmatic trial as confirmed by the PRECIS-2 rating of 42 out of 45 on the scale, with 0 corresponding to a fully explanatory study and 45 to a fully pragmatic study (cf. supplemental material) [24]. 

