## 6. Description of Study Intervention

### 6.1. Comparison Strategy: Control Group

The investigating physicians of the participating centers in the control group will be free to provide care as they see fit. However, a reminder of national and European guidelines for PE management will be given to them and they will have the recommendation to apply a validated strategy [3,4,5]. To make it easier, the different scores will be included in the clinical help–decision support software called SPEED [23]. Investigators will be asked to enter data about the included patients directly into SPEED, which will act as the study’s electronic case report form (eCRF). A paper version of the CRF will also be available. 

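### Physicians who know their centre's arm decide who is included, and the efficacy endpoint is imaging among those included; centre stratification and the known-result exclusion narrow a case-mix difference but do not control it.

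*Protocol article*

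**What the plan says.** Section 5 states: "SPEED&PEPS will be an open-labelled cluster-randomized study, with 10 centers being allocated to the control group and 10 centers to the interventional group". Before randomisation each centre measures its monthly volume of suspected PE and its imaging rate, and "These two criteria will be applied as stratification criteria during randomization to assure comparability between groups".

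Patients enter later, one at a time. Under section 4.1 they must have "Suspected PE due to thoracic symptoms (dyspnea, chest pain, or hemoptysis) and/or syncope without any other obvious explanation after clinical examination" and give "Free, prior, and informed consent to participate in the study". Section 4.2 excludes, in both arms, any patient with a "Known result of a specific diagnostic examination for PE (D-dimer test, thoracic CT angiography, pulmonary scintigraphy, or venous ultrasound of the lower limbs").

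The request to enter data differs by arm. Section 6.1 (control) says: "Investigators will be asked to enter data about the included patients directly into SPEED", with no timing. Section 6.2 (intervention) says: "Investigators will be asked to enter the information relating to patients included in the study directly into SPEED before performing any testing". Both sections allow a paper CRF.

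On the outcome, section 3.1 says: "The primary efficacy endpoint will be the rate of thoracic imaging among all included patients with suspected PE". Section 9.1 analyses everyone included, with one-sided tests. Section 9.2 specifies mixed-effects logistic regression for both primary endpoints and raises screening bias only in connection with missing data.

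**The concern.** Inclusion rests on an unblinded clinical judgement with no objective threshold, and it takes place in a centre whose arm is already known. If the arm influences who is called suspected, or who is asked for consent, the two groups differ in baseline risk before any diagnostic strategy has acted. The imaging rate depends heavily on baseline risk, so the primary efficacy comparison would mix two things: fewer scans in similar patients, and a different set of patients.

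One route is plausible. 4PEPS can end the work-up on clinical data alone (introduction and Table 1), so an intervention physician may include a very low-probability patient at little diagnostic cost. A control physician who sets PE aside at the bedside may not include that patient. The reverse is also possible: intervention physicians might not seek consent from patients they expect to score below 0.

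The difference in requested timing adds a second problem. Baseline items written down before testing in one arm, and at an unspecified time in the other, are a weak basis for checking or adjusting case mix afterwards.

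**Working it through.** **Who is protected from what**

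- Stratification (section 5) acts on centre volume and centre imaging rate, both measured before randomisation. It cannot act on patients recruited later.
- The known-result exclusion (section 4.2) applies to both arms and stops inclusion on the basis of a result. It concerns the result, not the order, so a control patient may still enter once a test has been requested. It does not limit additional low-risk inclusions in either arm.
- Blinded adjudication (sections 3.1 and 7) covers clinical events, not entry or imaging.

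**Inputs from the protocol**

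Control imaging 45%, target 36%, ICC 0.05, one-sided 5% (sections 9.1 and 10.2). 1280 patients per arm in 10 centres, so 128 per centre; safety rate 1.5%, margin 1.5 points, PE prevalence 14% (section 10.1).

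The target is consistent with itself: 0.45 × 0.80 = 0.36, a fall of 9 points. The stated 2128 patients do not reproduce at ICC 0.05. That is a separate matter, and nothing below depends on it.

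**Assumptions, not in the protocol**

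A share s of the intervention arm consists of added patients imaged at rate r. Practice is otherwise unchanged.

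**Formulas**

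- Intervention imaging rate: p1 = 0.45(1 − s) + r·s.
- Design effect: 1 + (128 − 1) × 0.05 = 7.35.
- SE = √{[0.45 × 0.55 + p1(1 − p1)] × 7.35 / 1280}.
- Rejection probability ≈ Φ[(0.45 − p1)/SE − 1.645].

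**Rejection probability with s = 10% and no true effect**

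| r | p1 | difference (points) | SE (points) | rejection |
|---|---|---|---|---|
| 0% | 40.5% | 4.5 | 5.30 | 21% |
| 5% | 41.0% | 4.0 | 5.30 | 19% |
| 10% | 41.5% | 3.5 | 5.31 | 16% |
| 20% | 42.5% | 2.5 | 5.31 | 12% |

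The nominal level is 5%. A smaller true ICC makes the inflation worse: at r = 5%, rejection is about 29% with ICC 0.02 and 39% with ICC 0.01.

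**Share needed to reproduce the full 9 points**

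s = 0.09/(0.45 − r).

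- r = 0%: 20% of the arm (256 of 1280).
- r = 10%: 26% (329 of 1280).
- r = 20%: 36% (461 of 1280).

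**Would it be seen?**

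If added patients had a PE prevalence of 1 to 2% (assumption), a 20% share gives 0.8 × 14% + 0.2 × (1 to 2%) = 11.4 to 11.6%, against 14%. A 10% share gives 12.7 to 12.8%, which is much harder to tell from chance.

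**Safety**

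With 10% extra patients who have no events, the rate is 1.5%/1.10 = 1.36%. That is a fall of 0.14 points against a margin of 1.5 points.

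**The case against.** The strongest reply is that the arms are treated more alike than the concern suggests. The inclusion wording is identical, consent must come first, and no patient in either arm may have a known PE test result. Section 6.2 asks when data on included patients are entered; it does not say whom to include, and it is a request, not an obligation. Control physicians are advised to use a validated strategy, and the introduction lists strategies that rule out PE on clinical criteria alone, so ending the work-up without a test is open to both arms. Section 12 justifies the cluster design by the risk of contamination. Covariates, screening logs and consecutive inclusion may stand in the full protocol or SAP.

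Much of this stands. It limits the claim to a risk that the described safeguards leave uncontrolled, and the point does not rest on an absent covariate list or log.

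Three stronger readings are tempting, and the documents do not support them:

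- That any bias favours 4PEPS on every comparison. No document figure fixes the direction, and opposite selection is equally conceivable.
- That case mix alone would deliver the target. This needs a fifth of the arm never to be imaged, or more than a third imaged at 20%.
- That section 5 claims comparability of patients. Its sentence follows a description of centres' baseline status and can fairly be read as being about centres.

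What the reply does not remove is that knowledge of the arm precedes a subjective entry decision that defines the primary denominator. Consecutive-inclusion wording elsewhere would not make that judgement blind.

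**Conclusion.** The point holds as an uncontrolled risk, not as a demonstrated bias. The plan relies on centre-level balance and a both-arm exclusion, neither of which governs who is recruited after allocation.

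The consequence falls mainly on the efficacy test. At ICC 0.05, a modest 10% share of lower-risk additions would raise the one-sided 5% error to about 12 to 21%. These figures rest on the assumed share and imaging rate, unchanged practice, equal centre sizes and a normal approximation. A shift in the other direction would hide a real effect instead.

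A reader might also infer that the non-inferiority conclusion is compromised; the 0.14-point movement does not support that. That randomisation precedes patient entry is implied by the design and by section 5 rather than stated outright.

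**What to change.** 1. Ask both arms to record inclusion and the objective clinical items (age, sex, history, heart rate, SpO2, symptoms), time-stamped, before any PE test is ordered. In control centres, use the paper CRF or an eCRF page that shows no score and no recommendation. This matters because section 12 reports that SPEED itself improves diagnostic management, so prompting its use before testing would change the usual-care comparator.
2. Pre-specify adjustment of both primary mixed-effects models for one patient-level summary of those items, for example the 4PEPS total without the subjective item on PE being the most likely diagnosis. Give the unadjusted result as a sensitivity analysis. Report the distribution of this summary, and PE prevalence, by arm. A single covariate suits the safety model, where about 1280 × 0.015 = 19 events are expected per arm.
3. State in section 5 that stratification balances centres, not patients recruited later.

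Do not restrict the efficacy analysis to totals of 0 or more: that would discard patients in whom 4PEPS is meant to avoid testing, and so remove real effect along with any bias.

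Cost: wording in the protocol and SAP, slightly more data entry in control centres, and a covariate-adjusted effect to interpret. Selection driven by suspicion that is never recorded will still be only partly controlled. The timing change has to be in place before the first patient, because baseline items not recorded in time cannot be recovered reliably.
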